### Safety Evaluation

The indicator of safety evaluation is the frequency of adverse events (AEs) arisen during the treatment course. For this trial, AEs related to acupuncture and EA mainly include unbearable pain, bleeding, haematoma, skin pigmentation, skin allergies, fainting/sweating/dizziness during acupuncture, or other uncomfortable symptoms. AEs related to medication mainly include gastrointestinal discomfort and drug allergies. AEs that occur throughout the study will be assessed and recorded and by the investigators. Investigators should also record the occurrence date, degree, duration, and treatment measures of AEs.

At occurrence of AEs, emergency measures will be taken in a timely manner. For serious AEs, the researchers should report to the principal investigator and ethics committee immediately, who will determine whether the participant should be withdrawn from the study.

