**Outcome assessment**						
(1) QST		○	○	○	○	○
(2) ZBPI		○	○	○	○	○
(3) Dosage of analgetic		○	○	○	○	○
(4) SF-36		○	○	○	○	○
(5) HADS		○	○	○	○	○
(6) PSQI		○	○	○	○	○
Safety assessment			○	○	○	○
Recurrence of PHN						○

*○, required; HADS, Hospital Anxiety and Depression Scale; PHN, postherpetic neuralgia; PSQI, Pittsburgh Sleep Quality Index; QST, Quantitative Sensory Testing; SF-36, Short Form 36 Health Survey; ZBPI, Zoster Brief Pain Inventory*.

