### Intervention

Participants will receive either EA combined with medication or medication alone.

The treatment course of both groups is up to 6 weeks and the follow-up period is 8 weeks.

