##### (2) Operation

Patients are asked to select the appropriate body position in terms of HZ sites, such as lateral, supine and prone positions, etc. The skin around the selected acupoint is routinely disinfected. Patients are then given acupuncture and deqi sensation is achieved in all acupoints. Two paired of acupoints (i.e., two Jiaji acupoints and two Ashi points, respectively) are connected to the EA apparatus. EA parameter is selected as dilatational wave and frequency is 2/100 Hz. EA intensity is determined according to patients' endurance.

Needles will be retained and EA will last for 30 min for each session. Patients will receive a total number of 30 EA sessions, with the frequency of 5 sessions per week for 6 weeks.

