#### Medication Group

Participants in the medication group will only receive oral administration of gabapentin capsule. The dosage of gabapentin starts from 100 mg Tid. 100–300 mg can be increased every 3–7 days and taken in three doses, but the total amount is not more than 1,800 mg/day. The dosage of gabapentin will be adjusted according to the patient's condition until his pain is effectively controlled.

After maintaining the medication for 2 weeks, the dosage can be gradually reduced and 100 mg can be reduced every 3–7 days.

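### The stated safety indicator stops with the treatment course, although adverse events are recorded to week 14 and assessed there

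*Protocol article*

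**What the plan says.** The Safety Evaluation section of the protocol article fixes the measure: "The indicator of safety evaluation is the frequency of adverse events (AEs) arisen during the treatment course". Later in the same paragraph it says: "AEs that occur throughout the study will be assessed and recorded". The Intervention section gives the periods: "The treatment course of both groups is up to 6 weeks and the follow-up period is 8 weeks".

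In Table 1, the row "Safety assessment" is marked at weeks 2, 4, 6 and 14. The treatment row is marked at weeks 2, 4 and 6 only. The table is not split by arm.

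On contact with staff, the Operation section says of the EA arm: "Patients will receive a total number of 30 EA sessions, with the frequency of 5 sessions per week for 6 weeks". The Medication Group section says of control: "Participants in the medication group will only receive oral administration of gabapentin capsule". The EA arm takes gabapentin on the same regimen.

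**The concern.** Safety is a headline aim: the abstract, introduction and conclusion all pair it with efficacy. The only named safety measure covers a shorter period than the one in which safety data are collected, and nothing says how the later data will be used. An analyst who follows the definition would report a frequency that omits the follow-up period, and another who follows Table 1 would report a different one. The choice could then be made after the data are seen.

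The boundary is also not firm. If gabapentin is still being taken after week 6, an event at week 8 may or may not belong to the treatment course, depending on which section is followed.

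A second issue arises once arms are compared. A frequency built from everything recorded at any time can depend on how often a patient meets staff, and the two arms differ in their stated treatment contacts.

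**Working it through.** **Inputs**
- Treatment up to 6 weeks, follow-up 8 weeks (Intervention).
- Safety assessments at weeks 2, 4, 6 and 14 (Table 1).
- EA: 5 sessions a week for 6 weeks (Operation).
- Gabapentin: start at 3 × 100 = 300 mg/day; increases of 100-300 mg at intervals of 3-7 days; ceiling 1,800 mg/day; 2 weeks of maintenance; then reductions of 100 mg at intervals of 3-7 days (Medication Group).

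**1. The plan's own figures.** 6 + 8 = 14 weeks, which matches the follow-up column of Table 1. 5 × 6 = 30 sessions, which matches the stated total.

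**2. What the indicator covers.** At most 6/14 = 43% of the time and 3 of 4 scheduled safety assessments. Outside it are 8/14 = 57% of the time and 1 of 4 assessments.

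**3. Can gabapentin run past week 6 (day 42)?** Assume that the steps are daily totals, that increases are the largest and all steps the fastest allowed, and that reduction follows maintenance and goes to zero. Days to zero = days up + 14 + days down.
- Peak 1,800 mg/day: (1,500/300) × 3 = 15; 15 + 14 + 18 × 3 = 83 days.
- Peak 900 mg/day: (600/300) × 3 = 6; 6 + 14 + 9 × 3 = 47 days.
- Peak 600 mg/day: (300/300) × 3 = 3; 3 + 14 + 6 × 3 = 35 days.

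If the first reduction falls on the day maintenance ends, each total is 3 days shorter: 80, 44 and 32. So at the fastest pace the 900 and 1,800 paths pass day 42 and the 600 path does not. With 7-day intervals the 600 path takes 7 + 14 + 42 = 63 days. Table 1 also assesses analgesic dosage at week 14, which is consistent with drug use after week 6 but does not prove it.

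**4. Observation by arm.**
- Scheduled safety assessments: 3 v 3 on treatment and 4 v 4 overall.
- Treatment contacts: 30 in the EA arm; none stated for control beyond the shared visits.
- If every gabapentin step needed a contact (an assumption), control would have 42/7 = 6 to 42/3 = 14 of them in 6 weeks. The EA arm would have the same ones, unless they were handled at EA sessions.

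The document does not say whether adverse events are asked about at EA sessions, so no size can be put on any reporting difference.

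**5. With the window extended.** 14 of 14 weeks and 4 of 4 assessments are used, equally in both arms. The sample size does not change.

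**The case against.** A treatment-period indicator can coexist with wider recording. The abstract promises assessment of all adverse effects during the trial. Events are recorded with date, degree and duration, so a split at week 6 can be derived later, and the serious-event reporting rule has no time limit. This stands. A reader might infer that late events will be discarded, but the document does not say so. It says only that the named indicator does not include them.

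The 57% is calendar time, not a share of risk. EA ends at week 6, and several of the listed EA events are procedural, such as bleeding or fainting during needling. This also stands, and it limits the practical size of the gap.

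The treatment course could be read to include gabapentin taken after week 6, which would bring those events inside the indicator. The Intervention section speaks against that reading, and under it the window would vary from patient to patient. The objection moves the ambiguity without removing it.

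Two stronger readings are tempting:
- One could set the 30 EA sessions against the on-treatment safety assessments and conclude that the EA arm is observed far more often for safety. Those are different things: Table 1 gives both arms the same safety schedule, and nothing says that events are elicited at EA sessions.
- One could read the separate lists of acupuncture-related and drug-related events as pre-sorting events for analysis. Both lists are worded as examples, and no analysis by list is specified.

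**Conclusion.** The point holds as a mismatch between the defined indicator and the data collected. It is modest in size but touches a headline aim. By the stated rule, 8 of 14 weeks and 1 of 4 scheduled safety assessments enter no named indicator. This takes the treatment course as up to 6 weeks, as the Intervention section and the treatment row of Table 1 have it.

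That gabapentin steps can pass week 6 follows from the Medication Group section under the assumptions shown. It is a tension with the Intervention section that has to be reconciled, not evidence that safety events will be lost.

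Unequal opportunity to report is a reasonable precautionary concern, given the difference in stated contacts. The document neither shows nor excludes such a bias. If it occurred through reports at EA sessions, it would raise the count in the EA arm.

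**What to change.** Redefine the safety indicator as all-cause adverse events and serious adverse events, by arm, from first study treatment to week 14, with weeks 0-6 and weeks 6-14 shown separately.

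Base the comparison of arms on patient-level incidence (patients with at least one event) from the shared assessments at weeks 2, 4, 6 and 14, asked in the same way in both arms. Report events noted at EA sessions separately.

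Reconcile the Intervention and Medication Group sections on when drug treatment ends, so that the treatment course has one meaning. Which clinical rule applies is for the investigators to settle.

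The cost is wording in the protocol, the case report form and the analysis plan. No visits or patients are added. The downside is that the reported adverse event rate may rise slightly, because more of the recorded events count.

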### Quality Control

Prior to the beginning of enrollment, in order to avoid treatment bias induced by different understanding of acupuncture methods from different researchers, one experienced acupuncturist will be selected from each sub-center, who should have at least 5 years of acupuncture clinical experience, to receive intensive training on acupuncture treatment procedure based on the treatment regimen. Meanwhile, all outcome assessors will attend standard training to practice outcome assessments and fill in the case report forms uniformly.

Throughout the trial, all study data will be collected in the case report forms and double entered into the electronic data capture system by independent researchers in due time. Dropouts or withdrawals from the trial will be recorded in details. A data safety monitoring committee according to the guidance of Data Safety Monitoring Board will be employed. Staffs in the committee will be responsible for monitoring the data and have the right to reveal blinded data. They will also verify the authenticity between the raw data and the recorded data. Besides, the principal investigator and other research team members from different centers will meet every 3 month to discuss issues arisen during the trial the best solutions.

Lastly, in order to promote enrollment and participant compliance, all treatment cost and all outcome measurements will be free for participants.

### Sample Size Estimation

The participants will be assigned to 2 groups in a ratio of 1:1. The sample size is calculated based on the change of ZBPI from baseline to 6 weeks after intervention, the results of which are acquired from our pilot study. It is assumed that n_1_ = n_2_, α = 0.05, and β = 0.2. Thus, each group approximately requires 57 participants. With an estimated dropout rate of 15%, a total of 132 subjects are needed, with 66 participants in each group.

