## Abstract

**Introduction:** The efficacy of conventional treatments for treating postherpetic neuralgia (PHN) remains unsatisfactory. Thus, this multicentre, randomized controlled, assessor-blinded trial aims to investigate the efficacy and safety of electroacupuncture (EA) therapy in patients with PHN.

**Methods and Analysis:** This multicentre randomized controlled trial will enroll 132 patients with PHN from 3 hospitals. All patients will be randomly assigned to either the EA combined with medication group or medication group through a computerized central randomization system in a 1:1 ratio. Outcome measures will be assessed before intervention, at 2, 4, 6 weeks after intervention and at the end of 8-week follow-up. Primary outcomes will be sensory thresholds and pain intensity. Secondary outcomes will include dosage of analgetic, quality of life, anxiety, and depression severity and sleep quality. All adverse effects will be assessed during the trial.

**Conclusions:** This study will provide evidence to ascertain whether EA is effective and safe for treating PHN.

**Ethics and Dissemination:** Ethics approval (No.ZSLL-KY-2017-025) has been obtained from the Ethics Committee of The Third Affiliated Hospital of Zhejiang Chinese Medical University. Informed consent will be signed prior to subject enrolment. The results will be submitted to international peer-reviewed journals and presented at international conferences.

**Trial Registration Number:** The study protocol has been registered in the clinicaltrials registry with the identification code NCT04594226.

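### Minor: 132 patients at 15% dropout leave about 56 per group, not the 57 that the sample size statement says are required

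*Protocol article*

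**What the plan says.** The Sample Size Estimation section of the protocol article sizes the trial on one comparison: "The sample size is calculated based on the change of ZBPI from baseline to 6 weeks after intervention". Its design inputs are "It is assumed that n_1_ = n_2_, α = 0.05, and β = 0.2", with 1:1 allocation. From these it concludes that "each group approximately requires 57 participants", and the dropout step follows: "With an estimated dropout rate of 15%, a total of 132 subjects are needed, with 66 participants in each group". The Abstract repeats the total, stating that the trial "will enroll 132 patients with PHN from 3 hospitals".

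The section does not give the formula used for the dropout allowance. It also does not give the effect size, the standard deviation or the sidedness of the test.

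**The concern.** Three linked numbers (57 required, 15% dropout, 66 enrolled per group) should satisfy one relation: enrolled patients less dropouts should be at least the number required. They do not. A dropout rate is a share of those enrolled, so the enrolled number is the required number divided by the retained fraction, 0.85. Multiplying by 1.15 instead applies the 15% to the completers and gives too small a number.

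What is at stake is the accuracy of the published statement. At its own assumed dropout rate, the trial ends slightly below its own target, so the statement that 132 patients allow for 15% dropout is not true as written.

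**Working it through.** **Inputs**, all from Sample Size Estimation: 57 per group required (described as approximate), dropout 15%, 66 per group and 132 in total enrolled, α = 0.05, β = 0.2, 1:1 allocation.

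**Reproducing the stated figure**
- Required number × (1 + dropout): 57 × 1.15 = 65.55, rounded up to 66 per group, hence 132. This matches the stated figure.
- Doing the same on the total: 114 × 1.15 = 131.1, rounded up to 132 for an even split. This also matches.

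**Checking what 66 per group delivers**
- Per group: 66 × (1 − 0.15) = 56.1, against 57.
- In total: 132 × 0.85 = 112.2, against 2 × 57 = 114.

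**Number needed to keep 57 at 15% dropout**
- Per group: 57/0.85 = 67.06, rounded up to 68, so 136 in total.
- Rounding only the total: 114/0.85 = 134.1, rounded up to 135.

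**Dropout that 132 can absorb**
- 1 − 57/66 = 9/66 = 13.6%.

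**Effect on power.** The article gives too little to reproduce the 57, so this step needs assumptions: a two-sided 5% two-sample t-test, and exactly 80% power at 57 per group. The implied standardised difference is then 0.529.

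| Evaluable per group | Power |
|---|---|
| 57 | 80.0% |
| 56.1 | 79.4% |
| 56 | 79.3% |

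The normal approximation implies a difference of 0.525 and gives the same powers to one decimal place.

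**The case against.** The strongest reply is that this is immaterial. The 57 is described as approximate and the 15% as an estimate. The shortfall is about one patient per group, and the dropout that can be absorbed is only 15 − 13.6 = 1.4 percentage points lower than stated. No design or analysis decision turns on it. That stands, and it is why the point is minor.

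The word *approximately* can also be pressed further. If the 57 was rounded up from an unrounded requirement between 56.0 and 56.1, division by 0.85 would itself give 66, because 66 × 0.85 = 56.1. That is possible, but the window is a tenth of a patient wide, and multiplication by 1.15 yields 66 directly. More generally, if 57 was rounded up from somewhere between 56 and 57, power at 56 lies between about 79.3% and just under 80%, so 79.3% is the low end of that range.

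It is also fair to say that the formula is inferred from a numerical match and not stated. The core point does not depend on it: by whatever route 66 was reached, 66 less 15% is below 57. Nor is this a detail that a condensed article leaves to a fuller document, since the conflict is among numbers the article itself prints.

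**Conclusion.** The statement is inconsistent as written, by a small amount: about 56 evaluable per group against about 57. Under the assumptions given in the working, the cost is under one percentage point of power. The inconsistency itself rests only on the printed figures. The explanation by a factor of 1.15 is the likely one but remains an inference, and the consistent total is 135 or 136 depending on rounding.

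Two stronger readings should be resisted. A reader might infer that the trial is materially underpowered; a loss of 0.6 to 0.7 points does not support that. A reader might also infer that the shortfall comes on top of further losses, from the Elimination Criteria and from a complete-case analysis. The documents do not support this either. The Elimination Criteria do remove participants for withdrawal, non-adherence or incomplete data, but nothing says these are additional to the 15%, and withdrawals are dropouts already, so adding them risks counting them twice. The Statistical Analysis section does not state a complete-case analysis.

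**What to change.** Keep 132 and restate the dropout sentence in one of two ways:
- 132 patients (66 per group) keep 57 per group with dropout up to about 13.6%; or
- at 15% dropout about 56 per group remain, with power about 79%, naming the test and sidedness on which that figure rests.

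Either costs one sentence and leaves recruitment and the Abstract unchanged. The stated allowance or power becomes slightly less favourable. If the team prefers to hold both 57 per group and 15% dropout, the target becomes 68 per group and 136 in total (135 if only the total is rounded up). That is three or four more patients, and the Abstract would have to change with it. The size of the discrepancy does not demand this.

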### Statistical Analysis

Statistical analysis will be performed using SPSS 17.0 for Windows (SPSS Inc., Chicago, IL, USA) by third-party statisticians. For categorical data, it will be displayed as counts and percentages. Numeric data with normal distribution will be expressed as mean ± standard deviations, whereas data with skewed distribution as median with 95% confidence intervals. Between-group differences for dichotomous variables for the baseline characteristic, such as gender and ages, will be compared according to the Chi-square test. For data in normal distribution, repeated measures analysis of variance (ANOVA) will be used to perform within-group and between-group comparison by assessing change in continuous variables before and after intervention at different time-points. For data in skewed distribution, within-group and between-group comparison will be assessed using non-parametric test. A *P* value of <0.05 will be considered statistically significant.

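### The observed distribution, by no stated criterion, chooses between repeated-measures ANOVA and an unnamed non-parametric test for the primary outcomes, and neither is tied to the week-6 ZBPI contrast that sized the trial

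*Protocol article*

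**What the plan says.** The Statistical Analysis section sets a conditional rule for continuous outcomes. On one side, "For data in normal distribution, repeated measures analysis of variance (ANOVA) will be used" for comparisons within and between groups, applied to change at the different time points. On the other, "For data in skewed distribution, within-group and between-group comparison will be assessed using non-parametric test". The only threshold given is "A *P* value of <0.05 will be considered statistically significant".

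The section does not say how normality or skewness is judged, or whether the decision is taken per outcome, per visit, per arm or on pooled data. It does not name the non-parametric test, and it does not say which visit or contrast decides the trial. Under Primary Outcome Measures, both QST and ZBPI are changes assessed at baseline, weeks 2, 4 and 6, and the end of follow-up (week 14 in Table 1), so the rule applies to both.

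The Sample Size Estimation section is more specific: "The sample size is calculated based on the change of ZBPI from baseline to 6 weeks after intervention".

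**The concern.** A primary analysis should be one named comparison, fixed before anyone sees the data. Here the shape of the data selects the comparison, and the two candidates do not answer the same question. Repeated-measures ANOVA compares mean change across visits. A rank test compares orderings and is paired in this plan with medians as the summary. The headline result could therefore be either kind of quantity, at an unstated visit or averaged over visits.

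The trial was sized on a third, simpler quantity: the difference in ZBPI change at week 6. If that contrast is not the one tested, the planned 80% power describes an analysis that may never be run.

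Baseline ZBPI is collected on everyone but enters, at most, through subtraction. Adjusting for it as a covariate is normally more precise and costs nothing.

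Both branches also set within-group comparison beside between-group comparison. Within-group change mixes any treatment effect with natural course and with gabapentin adjustment, so it is not evidence for electroacupuncture.

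**Working it through.** **Inputs from the protocol article.** α = 0.05 and β = 0.2 ("It is assumed that n_1_ = n_2_, α = 0.05, and β = 0.2"); 1:1 allocation; "each group approximately requires 57 participants"; 15% dropout; total 132; sizing endpoint ZBPI change to week 6; five assessment occasions.

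**Not in the article, so assumed.** Two-sided test; effect and SD (the article says only "the results of which are acquired from our pilot study"); correlation between visits r = 0.3, 0.5 or 0.7, equal for all pairs; treatment effect of one third, two thirds, full and full size at weeks 2, 4, 6 and 14; the switch rule.

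**1. The plan's own figure.** 57 × 1.15 = 65.55, rounded up to 66 per group, 132 in total. This matches and is not in dispute here. The 57 cannot be derived forward without an effect and SD. Solved backwards, d = (1.960 + 0.842) × √(2/57) = 0.525 SD (0.466 if one-sided).

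**2. The analyses side by side.**
- Sizing: between-group difference in ZBPI change at one visit, week 6.
- If normal: repeated-measures ANOVA of change over several visits; no decisive visit, no baseline covariate named.
- If skewed: a non-parametric test, unnamed; no visit, no baseline covariate named.

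**3. Power at 57 per arm.** Set the SD to 1 at every visit and the week-6 difference to d = 0.525. The base signal is 0.525 × √(57/2) = 2.803. Divide by the SD of the quantity analysed; power ≈ Φ(result − 1.96). Values are for r = 0.3 / 0.5 / 0.7.
- Week-6 ANCOVA, variance 1 − r²: 2.94 / 3.24 / 3.92, so 84 / 90 / 98%. Simulated: 83 / 89 / 97%.
- Unadjusted week-6 change, variance 2(1 − r): 2.37 / 2.80 / 3.62, so 66 / 80 / 95%. Mann-Whitney on the same change, simulated: 63 / 77 / 94%.
- Repeated-measures main effect: mean effect (1/3 + 2/3 + 1 + 1)/4 = 0.75 of d, variance 1.25(1 − r): 2.25 / 2.66 / 3.43, so 61 / 76 / 93%. Simulated: 60 / 75 / 93%.

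**4. How far this depends on the assumptions.**
- If 0.525 is measured in SDs of the change score, unadjusted change has 80% power at every r. The ANCOVA variance ratio is (1 + r)/2, giving 2.803/√((1 + r)/2) = 3.48 / 3.24 / 3.04, so 94 / 90 / 86%. The repeated-measures main effect has 0.75 × 2.803 × √1.6 = 2.66, so 76% throughout.
- If the full effect were present from week 2, the repeated-measures main effect would have 2.803/√(1.25(1 − r)) = 3.00 / 3.55 / 4.58, so 85 / 94 / above 99%, more than week-6 ANCOVA. Its shortfall in step 3 therefore depends on a gradual build-up.
- With skewed (lognormal-type) data, simulated power is 82 / 88 / 96% for ANCOVA, 80 / 91 / 99% for Mann-Whitney on change and 60 / 72 / 89% for the repeated-measures main effect. The rank test then matches or slightly beats ANCOVA.

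**5. Can the branch decide the result?** With a true effect and normal data, the repeated-measures main effect and Mann-Whitney on change fall on opposite sides of 0.05 in about 6-21% of simulated trials. If the rank test is run on the raw week-6 score instead, the disagreement is 14-40% (normal and skewed data together).

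**6. Type I error.** A mechanical pre-test (Shapiro-Wilk at 5% in each arm, assumed) choosing between a t-test and Mann-Whitney on week-6 change gives 4.9-5.5%. Taking the better of the repeated-measures main effect and Mann-Whitney on change gives about 8%.

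**The case against.** The strongest reply is that the name of the rank test and the criterion for skewness are details usually left to a statistical analysis plan, which is not shown. In addition, the analysis is done by third-party statisticians blinded to allocation, and a mechanical switch keeps type I error near 5%. All of that stands as far as it goes. But an analysis plan that supplied the missing details would still have two possible primary analyses. It could reach one only by replacing the stated rule. Blinding limits choosing by result; it does not settle which effect is being estimated.

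Three stronger readings are tempting and are not supported.
- *The ANOVA would seldom be used, because bounded pain scores fail normality tests.* The stated trigger is skewness, not any departure from normality. Rejection of integer scores by a general normality test can largely reflect rounding, and the ZBPI scoring is not in the text shown.
- *The analysis as a whole loses baseline and visit structure.* The ANOVA branch keeps the visits and works on change from baseline. For the rank branch the loss is an inference from common practice, since the text does not exclude a test on change scores. Medians with confidence intervals are also planned, so that branch has some descriptive estimate.
- *The switch inflates error through repeated testing over visits.* That inflation would come from testing several visits at 0.05 with any test. It is separate from the switch, and the article does not say that visits are tested separately.

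**Conclusion.** The concern holds in this form: a stated, data-dependent rule without a criterion selects between two analyses with different targets for the primary outcomes. Neither is the week-6 contrast used for sizing, and neither is said to adjust for baseline. The damage is an undefined estimand, room for choice and lost precision, not gross error inflation.

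Under normal data, 57 per arm, d = 0.525 on the week-6 SD, a gradually building effect and correlation 0.3 / 0.5 / 0.7, week-6 ANCOVA gains 20 / 12 / 3 percentage points of power over a rank test on change (83 − 63, 89 − 77, 97 − 94). Against the repeated-measures main effect it gains 23 / 14 / 4 (83 − 60, 89 − 75, 97 − 93). The gain over the unadjusted week-6 mean change follows from the variance ratio (1 + r)/2 and does not depend on the time course. The gain over the repeated-measures effect does depend on it, and the gain over the rank test disappears or reverses slightly under marked skew. None of these assumptions can be checked from the article. The case for a single fixed analysis does not rest on them.

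**What to change.** Replace the conditional rule for ZBPI with one primary analysis used whatever the distribution: the between-group difference at week 6 adjusted for baseline ZBPI, by ANCOVA or as the week-6 contrast of a mixed model over all visits. This is the contrast on which the sample size rests. Name one rank-based analysis, with its visit and variable, as a sensitivity analysis that cannot replace the primary result. Report within-group changes descriptively, and state that they are not evidence of efficacy.

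The cost is wording in the protocol and analysis plan, agreed before outcome data are examined. It needs no extra participants, visits or measurements, and no figure in the sample-size section changes.
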